# Postoperative complications and mobilisation following major abdominal surgery with vs. without fitness tracker-based feedback (EXPELLIARMUS): study protocol for a student-led multicentre randomised controlled trial (CHIR-*Net* SIGMA study group)

**DOI:** 10.1186/s13063-020-4220-8

**Published:** 2020-03-23

**Keywords:** Wearable fitness trackers, Postoperative complications, Major abdominal surgery, Quality of life, Recovery of function, Comprehensive Complication Index (CCI), Mobilisation, Postoperative outcomes, Dindo-Clavien, Randomised controlled trial

## Abstract

**Background:**

Postoperative complications following major abdominal surgery are frequent despite progress in surgical technique and perioperative care. Early and enhanced postoperative mobilisation has been advocated to reduce postoperative complications, but it is still unknown whether it can independently improve outcomes after major surgery. Fitness trackers (FTs) are a promising tool to improve postoperative mobilisation, but their effect on postoperative complications and recovery has not been investigated in clinical trials.

**Methods:**

This is a multicentre randomised controlled trial with two parallel study groups evaluating the efficacy of an enhanced and early mobilisation protocol in combination with FT-based feedback in patients undergoing elective major abdominal surgery. Participants are randomly assigned (1:1) to either the experimental group, which receives daily step goals and a FT giving feedback about daily steps, or the control group, which is mobilised according to hospital standards. The control group also receives a FT, however with a blackened screen; thus no FT-based feedback is possible. Randomisation will be stratified by type of surgery (laparoscopic vs. open). The primary endpoint of the study is postoperative morbidity within 30 days measured via the Comprehensive Complication Index. Secondary endpoints include number of steps as well as a set of functional, morbidity and safety parameters. A total of 348 patients will be recruited in 15 German centres. The study will be conducted and organised by the student-led German Clinical Trial Network SIGMA.

**Discussion:**

Our study aims at investigating whether the implementation of a simple mobilisation protocol in combination with FT-based feedback can reduce postoperative morbidity in patients undergoing major abdominal surgery. If so, FTs would offer a cost-effective intervention to enhance postoperative mobilisation and improve patient outcomes.

**Trial registration:**

Deutsches Register Klinischer Studien (DRKS, German Clinical Trials Register): DRKS00016755, UTN U1111-1228-3320. Registered on 06.03.2019.

## Background

Postoperative morbidity, mortality and patient-reported outcomes are arguably the most relevant outcome parameters in surgery, enabling a full risk-benefit assessment of surgical interventions. Although mortality for major abdominal surgery has decreased significantly over the last decades, morbidity remains high [1–4]. Complication rates between 30 and 60% have repeatedly been reported in randomised controlled trials (RCTs) for pancreatic [5–8], hepatobiliary [9], colorectal [10–12] and upper gastrointestinal surgery [13–15]. Interestingly, non-surgical complications like pulmonary and cardiac complications constitute a substantial part of overall morbidity [13].

Postoperative ambulation/mobilisation has been postulated to decrease postoperative complications in abdominal surgery and is part of all Enhanced Recovery After Surgery (ERAS) guidelines [16, 17]. However, the quality of the evidence to support this recommendation is very low [18–21]. Therefore, it is still unknown whether early and enhanced mobilisation can independently improve outcomes after major abdominal surgery and, if so, how this is best implemented in daily clinical practice [22].

Although designed as a consumer product to help motivate individuals to be physically active, wearable fitness trackers (FTs) are becoming increasingly popular as measurement tools in clinical research [23]. Importantly, FTs can be used to objectively measure outcomes like steps or distance covered and can thus be used as a feedback tool to meet prespecified mobilisation targets through feedback via the FT display. Few trials have studied FTs in the postoperative setting, and none used standardised assessment of postoperative complications as a primary outcome measure [24–29].

### Rationale for the trial

The high rate of postoperative complications following major abdominal surgery warrants clinical trials that investigate interventions which could potentially reduce postoperative morbidity. Early and enhanced postoperative mobilisation has been advocated to reduce postoperative complications, but it is still unknown whether it can independently improve outcomes after major abdominal surgery. FTs are a promising tool to improve postoperative mobilisation following major abdominal surgery, but their effect on postoperative complications and recovery has not been studied in high-quality clinical trials.

### Study aims and objectives

The objective of this study is to determine whether daily step goals and feedback via a FT reduces the rate of postoperative complications following elective major abdominal surgery.

### Student-led clinical research

The teaching of clinical research and its associated scientific methodology is underdeveloped in medical schools, leading to an expected deficit in academic faculty across Europe [30, 31]. Research-based learning is a concept that refers to a trend in higher education: to provide students with the opportunity to gain knowledge by conducting their own scientific inquiries or investigations [32]. In 2017 the study network of the German Surgical Society (CHIR-*Net* [33];) founded a student-led clinical trial network across Germany (SIGMA; Student-Initiated German Medical Audit, [34]) [35, 36]. SIGMA has performed an observational study investigating patient-reported outcome measures and complications after surgery [37] and will perform the EXPELLIARMUS trial. To our knowledge, this is the first multicentre RCT ever to be performed by medical students.

## Methods/design

### Trial design

EXPELLIARMUS is a multicentre RCT with two parallel study groups.

### Requirements for participating centres

Participating trial centres require at least one investigator (surgeon) and at least two medical students who are acquainted with the trial protocol and electronic case report form (eCRF). Furthermore, approval from the local ethics committee according to respective rules and regulations is mandatory.

### Recruitment of study sites

Fifteen regional centres of the clinical trial network (CHIR-*Net*, [33]) have committed to participate in the EXPELLIARMUS trial; all are university hospitals or tertiary care centres in Germany.

### Participants

#### Preoperative inclusion criteria

Participants must fulfil the following criteria:
Patients scheduled for elective major abdominal surgery defined as procedures expected to last more than 2 h, or with an anticipated blood loss greater than 500 ml [38]Ability to understand the character and individual consequences of the clinical trialOpen or laparoscopic or robotic surgery or any variant (laparoscopic-assisted, hybrid procedures, etc.)Provision of written informed consentAge ≥ 18 years.

#### Preoperative exclusion criteria

The preoperative exclusion criteria are as follows:
American Society of Anesthesiologists (ASA) grade > 3Preoperative immobility or inability to walk unaidedParticipation in another interventional trial with interference of intervention and outcome of this studyExpected postoperative stay in the intensive care or intermediate care ward ≥ 4 daysPlanned re-operation within 30 days after index operationPlanned abdominal-thoracic operations (two-field surgeries).

#### Intra/postoperative inclusion criteria

The intra/postoperative inclusion criteria are as follows:
Expected postoperative stay on intensive care or intermediate care ward of less than 4 daysNo planned re-operation within 30 daysConfirmed major abdominal surgery (as defined in “Preoperative inclusion criteria”).

### Intervention

In the experimental group, patients are fitted with a wearable FT (ActiGraph GT9X Link, ActiGraph, ProCare, Groningen, the Netherlands) on their dominant wrist after the operation for the duration of their postoperative stay until discharge or a maximum of 30 days. If the FT cannot be placed on the dominant wrist, it should be fitted on the non-dominant wrist. If this is also not possible, the FT should be fitted to any part of the patient’s body with a clip. Patients receive real-time visual feedback via the display of their tracker regarding daily steps taken and are encouraged to meet predefined daily step goals. In addition, ambulation is encouraged by the interprofessional care teams to meet predefined step goals.

The predefined step goals/instructions (mobilisation protocol) are as follows:
“Please ambulate/mobilise as much as possible and allowed by your doctors”“Please take more steps than yesterday”“Your daily step goal should be 4000 steps per day or more. Don’t worry if you do not reach this goal immediately”“You should reach this daily 4000-step target latest on postoperative day 5 in the case of laparoscopic surgery or on postoperative day 8 in the case of open surgery”.

In the control group, patients are fitted with a wearable fitness tracker (ActiGraph GT9X Link, ActiGraph, ProCare) on their dominant wrist for the duration of their postoperative stay until discharge or a maximum of 30 days. The display of the device is disabled (blackened), and accordingly no feedback via the device is given. Patients are allowed to mobilise at will, i.e. as tolerated. If possible, mobilisation is performed according to ERAS guidelines on the morning of postoperative day 1 (POD 1) or according to in-house regimes [18, 19, 21]. Ambulation is encouraged by the interprofessional care teams according to local standards (current practice), but no specific mobilisation protocol is provided.

### Assignment of intervention and randomisation

In order to achieve comparable study groups, patients will be randomly assigned to one of the two groups using a centralised web-based tool (www.randomizer.at). The online randomisation procedure provides information regarding the group allocation. Block randomisation with variable block sizes is used. Randomisation will be stratified by type of surgery (laparoscopic vs. open). Laparoscopic-assisted or hybrid procedures are counted as laparoscopic surgeries. Conversions from laparoscopic to open surgery are counted as open procedures. Randomisation will be performed on the day of surgery (visit 2) at the time of skin closure or later. Randomisation will be carried out only if all intraoperative inclusion criteria are fulfilled (see above). The online randomisation tool ensures concealment of the randomisation schedule. It is a computer-generated, concealed schedule that is not accessible by any trial participant or investigator. Randomisation will only be done by authorised trial personnel (investigator, medical student or designated representative) with their login data. Patients are recruited to the trial at least 24 h before surgery.

### Blinding

Neither patients nor outcome assessors will be blinded to the intervention, as this is unfeasible and contradicts the pragmatic character of the trial. However, given the objective nature of the primary and most secondary endpoints, the risk of bias is limited.

### Withdrawal

Patients may decide to withdraw from the study at any time without providing any specific reason for their decision. If, in the investigator’s opinion, continuation of the trial intervention would be detrimental to the subject’s well-being, the FT-based feedback will be discontinued (screen blackened). In addition, the feedback by the interprofessional care team will be discontinued, and the patient will not receive any more step goals. In both cases, the reason for withdrawal must be recorded in the CRF and in the patient’s medical records. If patient enrolment is unsatisfactory with respect to quality or quantity, or data recording is severely inaccurate or incomplete, as well as if externally respective evidence is given, the trial may be prematurely closed by the coordinating investigator in consultation with the responsible statistician and the CHIR-*Net* SIGMA steering committee. If the FT is removed, breaks or is otherwise unavailable, the clinical investigators will seek to replace it as soon as possible to guarantee complete step counts.

### Outcome measures

The primary endpoint of the study is defined as postoperative morbidity measured via the Comprehensive Complication Index (CCI) [2, 3] within 30 days after the index operation. The CCI is calculated for an individual patient based on the assessment of all complications according to the Dindo-Clavien classification [39, 40]. This classification grades postoperative complications according to their sequelae and has gained universal acceptance. Although it allows for an objective assessment of complications, it provides neither definitions of complications nor a measure of the entire impact of complications for an individual patient. The latter is addressed by the CCI, which measures the overall morbidity for an individual patient on a scale from 0 (no complication) to 100 (death). The CCI summarises all postoperative complications instead of focusing on specific complications and is thus an objective measure to assess the full burden and impact of complications in a single patient [39, 40].

The following secondary endpoints will be assessed in the EXPELLIARMUS trial:
Number of steps for each POD until POD 8 or until discharge, whichever comes first. This serves as a measure of success for the trial intervention.Patient-completed quality of recovery assessment according to Quality of Recovery 15 (QoR-15) at baseline and on POD 4 (or at discharge, whichever comes first) [41, 42]. QoR-15 is a validated short-term measure of postoperative recovery with 15 questions [41]; it has been developed from the longer QoR-40 [42]. It covers some, but not all aspects of postoperative recovery that are important to patients and experts [38]. As for the QoR-40, it can be assumed that QoR-15 results normalise within a week after major abdominal surgery [43]; thus, assessment at baseline and on POD 4 seems reasonable to elucidate potential differences between the two groups.Activity data (via the wearable device for each POD until discharge or a maximum of 30 days):
Metabolic equivalents of tasks (METs) ratesEnergy expenditureRaw accelerationActivity and sedentary boutsPhysical activity intensityTotal sleep time.

These data are provided by the FT used in the EXPELLIARMUS trial and allow correlating activity data with clinical outcomes for exploratory analyses.


### Patient time line

All consecutive patients are screened preoperatively and are enlisted in a screening list. Reasons for non-enrolment must be stated. Patients are enrolled given their ability to understand the extent and nature of the trial, their written informed consent after detailed patient information and fulfilment of all preoperative inclusion and exclusion criteria. Baseline data are collected during screening/baseline visit. Surgical data are collected during visit 2. Primary and secondary outcome parameters are collected during visits 3–8 within 30 PODs. Table 1 gives an overview of data items and activities for each trial visit.

**Table 1 Tab1:** Trial visits, data items and activities of the EXPELLIARMUS trial

Activity	Visit 1 (screening, enrolment)	Visit 2 (surgery, POD 0)	Visits 3–6 PODs 2, 4, 6, 8 (respective visits are omitted if patient has been discharged before)	Visit 7 (at discharge, ± 1 day)	Visit 8 (POD 30 ± 4; end of study or premature study termination)
Data items					
Demographics and baseline data	X				
HRQoL (EORTC QLQ-C30)	X		X (only POD 8 = visit 6)		X
Quality of recovery (QoR-15)	X		X (only POD 4 = visit 4)		
Surgical and anaesthesiological data		X			
Assessment of postoperative complications (according to Dindo-Clavien)			X	X	X
Assessment of re-operation			X	X	X
Assessment of bowel function^a^			X	X (only if no bowel function during previous visits)	
Assessment of postoperative pulmonary complications^b^			X	X	X
Assessment of pulmonary embolism			X	X	X
Assessment of deep vein thrombosis			X	X	X
Assessment of pain (NRS)			X	X	
Unintended fall/collapse			X	X	
Assessment of nasogastric tube, drains, urinary catheters			X (until removed)	X (until removed)	X
Assessment of physiotherapy and assisted mobilisation			X	X	X (only if patient is still in hospital)
Assessment of mobilisation target (step goal)			X	X	X (only if patient is still in hospital)
Length of hospital stay				X	X^c^
Discharge destination				X	
Activity items					
Physical activity (DASI)^d^	X				
Instruction FT	X				
Contact information for later visits	X				
Randomisation (postoperative)		X			
Attachment of FT		X			
6-MWT			X (only POD 6 = visit 5)		
Communication of step goals in the interventional group			X		
Assessment of FT (e.g. battery)			X		
Collection of FT and data transfer				X	X^c^

*6-MWT* 6-min walking test, *DASI* Duke Activity Status Index, *EORTC QLQ-C30* European Organisation for the Research and Treatment of Cancer Quality of Life Questionnaire C30, *FT* fitness tracker, *NRS* numeric rating scale, *HRQoL* health-related quality of life, *QoR* quality of recovery, *POD* postoperative day

^a^Via the GI-2 score defined as “The patient has tolerated solid intake (no vomiting) for 24 h AND has passed stool” [46]

^b^Via the Melbourne group score [13]

^c^If patient has not been discharged since index surgery

^d^Via the Duke Activity Status Index [49]

### Visit 1 (preoperative, informed consent)

All consecutive patients are screened for potential inclusion. Eligible patients are asked for informed consent. Enrolled patients are instructed on how to use the wearable FT (see “Intervention”). In addition, the following data items will be collected: (1) demographic data; (2) baseline data; (3) medical history/comorbidities; (4) HRQoL (EORTC QLQ-C30) [44]; (5) baseline functional data via the QoR-15 questionnaire [41, 42]; (6) status of physical activity via the Duke Activity Status Index (DASI) [49].

### Visit 2 (day of surgery, postoperative day 0)

On the day of surgery, data concerning the performed procedure are collected, including duration of surgery, blood loss, type of surgery and type of surgical access (open vs. laparoscopic). Furthermore, data regarding number and types of abdominal drains, nasogastric tubes, urinary catheters and postoperative analgesic are collected. At this time, randomisation will be performed (see above) and the wearable FT is attached.

### Visits 3–6 (postoperative days 2, 4, 6 and 8 (± 1 day))

Visits 3–6 have equivalent contents with the exception of the QoR-15 questionnaire, which is only administered at visit 4, the 6-MWT, which is performed only at visit 5 (or at discharge, whichever comes first) and HRQoL assessment (EORTC QLQ-C30), which is only performed at visit 6. If the patient is discharged before undergoing visits 3–6, the respective visits are skipped and the discharge visit (visit 7) is performed.

Visits 3–6 include assessment of postoperative complications according to Dindo-Clavien (primary endpoint). In addition, all secondary endpoints will be assessed. Furthermore, data on physiotherapy and mobilisation support by health-care team members other than physiotherapists (e.g. nursing staff) are collected. Finally, patients in the experimental group receive instructions about their step goals, and it is assessed whether these mobilisation targets have been met since the last visit.

### Visit 7 (day of discharge, ± 1 day)

On the day of discharge, the FTs are collected, and the data are read out and transferred over a secure upload server. Furthermore, all data items of visits 3–6 will be assessed. Finally, the discharge destination from the hospital needs to be documented. If discharge occurs before visit 5, the 6-MWT test needs to be performed at visit 7.

### Visit 8 (postoperative day 30 (± 4 days) or premature study termination)

If the patient has not been discharged, a clinical visit will be performed. In case of prior discharge, either a telephone visit can be performed or the patient can be seen in the outpatient clinic. Assessments include complications and re-operations, pulmonary complications, pulmonary embolism or deep vein thrombosis, duration of drain placements, the health-related quality of life questionnaire EORTC QLQ-C30 and data on potential physiotherapy. If the patient is still in hospital, the FTs are collected, and the data are read out and transferred over a secure upload server.

### Sample size calculation

The sample size calculation is based on the primary endpoint “CCI within 30 days after the index operation”. Assumptions are based on the literature [39, 40, 50]: a decrease of the CCI by 10 points is considered relevant by patients and clinicians (minimal important difference, [40]) and a conservative standard deviation of 20 is assumed. The CCI in major abdominal surgery (control intervention) is assumed to be 22 [39, 40]. We hypothesise to decrease the CCI by 10 points in the interventional group (minimal important difference, [40]). The primary endpoint is tested simultaneously using a two-sided *t* test in the subgroup of patients with a minimally invasive surgery and the subgroup of patients experiencing an open surgery. The ratio of minimally invasive to open is expected to be 1:1. Therefore, the overall two-sided significance level of α = 0.05 is adjusted by Bonferroni correction, yielding α = 0.025 for each of the two subgroups. Thus, to achieve a power of 80%, a sample size of *n* = 156 (78 per group) has to be recruited per subgroup with a total required sample size of the trial of *n* = 312 (156 per therapy group). To compensate for drop-outs and lost-to-follow-ups, a further 10% of patients will be randomised, leading to a total sample size of *n* = 348 (174 per group). Patients who die during the observation period receive the maximum number of 100 CCI points per definition [39, 40].

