### Statistical analysis

For the examination of the primary endpoint “CCI within 30 days after the index operation”, the hypotheses to be assessed for each subgroup (minimally invasive or open) in the primary analysis are as follows: H0: μ1 = μ2 vs. H1: μ1 ≠ μ2, where μ1 and μ2 denote the mean CCI in the control and the intervention group respectively. The significance level is set to a two-sided α = 0.025 per subgroup test. Due to the stratified randomisation and relatively large number of centres in relation to the sample size, inclusion of centre as a random effect is recommended [51]. Therefore, the primary endpoint will be examined in the respective subgroup (minimally invasive or open) using a linear mixed model including centre as random intercept and group as fixed effect, which leads to equal or even increased power as compared to using a conventional two-sided *t* test [52].

The primary analysis will be conducted based on the full analysis set according to the intention-to-treat (ITT) principle and comprises all patients in the group they were randomised to. In the ITT analysis, missing data for the primary outcome variable will be replaced by using multiple imputation, which takes the covariates treatment group and centre into account by application of the fully conditional specification method [53]. The per protocol (PP) set consists of all patients treated per protocol; no missing data will be imputed. An additional mobility population consists of all patients who were randomised, had no re-operation within 30 days and had not been on the intensive or intermediate care ward for ≥ 4 days during the first postoperative week.

In general, for the full analysis set, all baseline values and secondary outcomes will be evaluated descriptively, and descriptive *p* values are reported together with 95% confidence intervals for the corresponding effects. Thereby, secondary endpoints will be evaluated descriptively using regression models including group as fixed effect and centre as random intercept as specified for the primary endpoint.

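### The SD of 20 is not conservative beside a control mean CCI of 22, so 80% power per access subgroup is conditional on the SD and on a 1:1 access split

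*Protocol article*

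**What the plan says.** In the section Sample size calculation, "The CCI in major abdominal surgery (control intervention) is assumed to be 22", the target is stated as "We hypothesise to decrease the CCI by 10 points in the interventional group", and "a conservative standard deviation of 20 is assumed". The primary endpoint is tested separately in minimally invasive and open surgery, and "the overall two-sided significance level of α = 0.05 is adjusted by Bonferroni correction". The Statistical analysis section agrees: "The significance level is set to a two-sided α = 0.025 per subgroup test". The result is 78 per group, 156 per subgroup, 312 in total, and 348 after a 10% allowance for losses. On access, "The ratio of minimally invasive to open is expected to be 1:1".

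Two other places bear on the SD. Outcome measures sets the CCI scale at 0 without a complication and 100 at death. The Background says: "Complication rates between 30 and 60% have repeatedly been reported in randomised controlled trials".

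**The concern.** The CCI has a block of patients at exactly 0. Once a mean and a share of patients with any complication are given, the SD has a mathematical minimum. An SD can be called conservative only if it lies comfortably above that minimum. Here it lies below it over most of the complication range that the article cites, and only a little above it at the top.

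The 80% also applies to each of two co-primary tests, so it depends on the size of each access stratum. Stratified randomisation balances the arms within a stratum but does not fix how many patients fall in each, and conversions are counted as open. If either assumption fails, the power of at least one primary test is below the figure stated without qualification.

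**Working it through.** **1. The plan's own figure.** Inputs from Sample size calculation: difference 10, SD 20, two-sided α = 0.025, power 80%.

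- Normal approximation: n = 2(2.2414 + 0.8416)² × (20/10)² = 76.04, rounded up to 77 per group.
- Exact noncentral t: 78 per group, power 80.4%.
- Four cells of 78 give 312. Losses: 156/0.9 = 173.3, so 174 per arm and 348 in total.

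The stated numbers are right on their inputs.

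**2. Minimum SD in the control arm.** Let p be the share of patients with any complication, m the arm mean, and s the SD of CCI among patients with complications. Uncomplicated patients score 0, so

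Var = p[s² + (m/p)²] − m², and with s = 0 the minimum SD is m√((1−p)/p).

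With m = 22:

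| p | Mean CCI among complicated (22/p) | Minimum control SD |
|---|---|---|
| 30% | 73.3 | 33.6 |
| 40% | 55.0 | 26.9 |
| 45% | 48.9 | 24.3 |
| 50% | 44.0 | 22.0 |
| 54.8% | 40.2 | 20.0 |
| 60% | 36.7 | 18.0 |

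The threshold for SD 20 is p = 484/(484 + 400) = 0.5475. Above it, the largest s compatible with SD 20 is √{[400 − 484(1−p)/p]/p}. This is 2.7 at 55% and 11.4 at 60%, on a scale where a death scores 100.

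**3. Pooled SD.** The t test uses both arms, and the intervention mean is 22 − 10 = 12. How the effect arises is not stated, so two extremes are shown, both with s = 0:

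- Fewer complications at equal severity: pooled variance = 374/p − 314. Minimum pooled SD is 22.7 at 45%, 20.8 at 50% and 17.6 at 60%.
- Same share, lower severity: pooled variance = 314(1/p − 1). Minimum pooled SD is 19.6 at 45%, 17.7 at 50% and 14.5 at 60%. An SD of 20 is possible from p of about 44%.

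The article gives no value for s. With s = 15 (assumed), the pooled SD is 24.4, 22.8 and 20.3 in the first case, and 22.0, 20.7 and 18.6 in the second, at 45%, 50% and 60%.

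**4. Power at 78 per arm** (difference 10, α = 0.025, noncentral t):

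| SD | Power | n per arm for 80% |
|---|---|---|
| 18 | 88.5% | 63 |
| 20 | 80.4% | 78 |
| 22 | 71.7% | 94 |
| 24 | 63.3% | 111 |
| 26 | 55.6% | 130 |
| 30 | 43.0% | 173 |

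**5. Access split at SD 20, 312 evaluable:**

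| Split | n per arm, smaller stratum | Power, smaller | Power, larger |
|---|---|---|---|
| 45:55 | 70.2 | 75.6% | 84.4% |
| 40:60 | 62.4 | 69.9% | 87.6% |
| 30:70 | 46.8 | 55.7% | 92.4% |

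If nearly all 348 are evaluable, power is about 5 points higher: at a 1:1 split (87 per arm), 84.9% at SD 20 and 76.9% at SD 22; in the smaller stratum at 40:60 and SD 20, 75.2%.

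**The case against.** The mean of 22 and the range of 30 to 60% come from different cited sources. The range is background, does not enter the calculation, and does not say which complications it counts. The CCI counts every complication, including grade I, so the share with a CCI above 0 could exceed 60%, and an SD of 20 would then be unremarkable. This stands. It means that the article does not prove the SD wrong. It does not make 20 conservative, because the article gives no complication share of its own and 20 is low against the only range it offers.

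A reader might infer that power is really 43% or less, from the SD minimum of 33.6 at a 30% rate. The documents do not support that. At 30 to 40%, a mean of 22 requires complicated patients to average 55 to 73 points, while the Discussion says that grade I and II complications add few points. In those cells the mean of 22 would be as doubtful as the SD.

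The pooled SD can also be 20 or less when the control-arm SD is larger, because the intervention arm has the lower mean. In addition, the analysis set is all randomised patients with multiple imputation, and few missing values are expected, so the figures at 78 per arm lean low. Both points stand and are built into the ranges above.

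A reader might also infer that a cap per stratum is missing. The section does require 156 per subgroup, and the mechanism may be in the full protocol, which is not shown. Its absence from the article is no finding.

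**Conclusion.** The point holds in limited form. There is no arithmetic error: 78, 156, 312 and 348 all reproduce. What fails is the description of the SD as conservative, and with it the unqualified 80% per subgroup. With a control mean of 22, an SD of 20 in the control arm is unattainable below a complication share of about 55%, and at 60% it leaves a within-complication SD of only about 11.

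The 80% holds if the pooled SD is really 20 and the split is 1:1. The first needs a complication share near or above the top of the cited range, or a smaller SD in the intervention arm. The second is only an expectation. Pooled SDs of 22 to 24 give 72 to 63% power, and a 40:60 split alone gives about 70% in the smaller stratum.

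The bound rests only on the scale and the stated mean. The pooled figures also rest on assumptions about how the effect arises and about the spread among complicated patients, neither of which the article gives. It would go too far to say that power is certainly below 80%, since the scenarios fall on both sides of it.

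**What to change.** Delete the word conservative. State that 80% per subgroup is conditional on a pooled SD of 20 and a 1:1 access split, and add a sensitivity table: at 78 per arm, 80% at SD 20, 72% at 22, 63% at 24, 56% at 26 and 43% at 30; in the smaller stratum at SD 20, 76% at 45:55, 70% at 40:60 and 56% at 30:70. Note that these rise by about 5 points if nearly all 348 are evaluable.

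Have the data manager, who according to Data management alone has database access during the trial, compute the allocation-blind SD of the CCI and the access split from the patients already included (219 at the date in Trial status). Report the power that they imply. The allocation-blind SD includes a small contribution from any treatment difference: with equal arms and a 10-point effect, it adds 5² = 25 to the variance, which should be noted.

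No increase in sample size is needed for this, and no stratum caps. If the split so far were 40:60, caps of 174 would need (174 − 87.6)/0.40 = 216 further eligible patients instead of the 348 − 219 = 129 remaining. At 30:70 the figure is (174 − 65.7)/0.30 = 361. The cost of the proposed change is a less favourable stated figure and one blinded calculation.
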